**Methods:**

This study is a single center, prospective, intervention randomized controlled trial with a control group. 174 patients of 18–35 years old with post-acute ankle sprain will be included. A randomized controlled study is conducted and divided into a control group and an experimental group. The control group receive routine treatment, while the experimental group receive integrated traditional Chinese and western medicine rehabilitation programs. The intervention lasted for a total of 2 weeks. The main outcome measures are Visual Analog Scale and Short Form McGill Pain Questionnaire; the secondary outcome measures are the Foot Ankle Ability Assessment Scale, AOFAS Ankle Posterior Foot Scale, torque and gait. This study protocol aims to evaluate the safety and effectiveness of integrated traditional Chinese and western medicine rehabilitation programs by comparing the results of two groups before and after treatment. This protocol will follow the SPIRIT guidance.

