## Methods

### Design

The study is a randomized controlled trial (RCT). A total of 174 post-acute ankle sprain patients will be recruited and randomly divided into the intervention group and the control group at a ratio of 1:1. Recruitment of eligible patients will begin from January 2025. Participants of the intervention group will be treated with TCAWM and participants of the control group will be treated with routine treatment. The whole study period will be 2-week including baseline and 2-week treatment. The study design is illustrated in the flow chart in Fig 1. The study protocol was approved by the Regional Ethics Review Committee of Shuguang Hospital (number: 2024-1535-118-01).

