### Outcomes measures

#### Primary outcomes

① Visual Analog Scale (VAS) [38,39]. VAS is used to evaluate the degree of pain. Draw a 10cm horizontal line on the paper with a starting point of 0 and a ending point of 10, marking 0 as painless and 10 as unbearable pain. Mark the corresponding scale every 1cm in the middle of the line. Ask the subjects to mark any position on the horizontal line based on their pain perception, as the degree of VAS pain in the subjects.

② Short form McGill Pain Questionnaire (SF-MPQ) [38,39]. SF-MPQ is used to evaluate pain sensation, with a total of 47 items. The first 11 items evaluate the degree of pain sensation (PRIA), and the 12–15 items evaluate the emotional state of pain (PRIB). The pain level of each item is described as painless (0 points), mild (1 point), moderate (2 points), and severe (3 points). In addition, both pain status and visual analogue scores are now included in the evaluation of overall pain status.

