### Follow up

There will be a follow-up plan to evaluate the long-term efficacy and safety of TCAWM and routine treatment when the protocol ends, the research will follow up the patients after 3 months of the treatment. Participants will not receive any intervene during follow-up. At the end of follow-up, the investigator will make a contract with patients by telephone, E-mail and etc. They will be asked to come to reception room and have a test about VAS、SF-MPQ、FAAM、AOFAS、Torque and gait.

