### Statistical analysis

For all outcomes, we will perform intent to treat analysis for our primary assessment of efficacy and a supplementary per protocol analysis. Use SPSS 21.0 statistical software for statistical analysis, including descriptive statistics such as mean, standard deviation. Quantitative data are analyzed using methods such as analysis of variance. Count data is analyzed using chi square test, Fisher’s exact test; Non parametric rank sum test and CMH chi square test is used for rank data. Set α = 0.05 as the significance test level, and when P<0.05, it indicates that the difference is statistically significant.

We will perform the following subgroup analyses: sex, men versus women; age, comparing outcomes for participants aged ≤30 versus >30; injury characteristic, non-sports versus sports injury; and grade 1 versus grade 2 sprain. To estimate significance of the subgroup treatment effect modification we use a Wald test of the treatment by subgroup interaction term from a logistic regression model.

To evaluate effects of missing data,we will employ appropriate data imputation methods to minimize bias. Specifically, we plan to use multiple imputation techniques, which allow us to create several complete datasets by filling in missing values based on observed data patterns. This approach will help us to better estimate the parameters of interest while accounting for the uncertainty associated with missing data.

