### Limitation

Despite the potential strengths, there are some limitations in our trial. Firstly, in this study, the intervention is a non-drug therapy, which cannot be ideally implemented in accordance with the provisions of double-blind. However, the strict management of researchers, data managers and statisticians in this study will help us to reduce performance bias. Secondly, the planned short treatment period to minimize dropout rates may affect the results of this study.Thirdly, due to insufficient preliminary data to determine the sample size, we have designed this experiment as a single center preliminary study. In addition, the sample selection for this protocol is between the ages of 18 and 35, further studies in various groups with a greater age range such as childern and olders are recommended. Fourthly, the patients cannot be blinded due to the particularity of treatment. Patients will know whether they had received additional treatment, which, in some cases, may have increase the risk of dropout in control patients. Finally, this is an exploratory study that does not involve long-term follow-up to observe long-term treatment outcomes and adverse reactions. For this reason,we will add a plan for participant follow-up after the protocol ends which could help assess the durability of intervention effects.

Nevertheless, the results of this study are expected to provide preliminary evidence on the effectiveness and acceptability of the integrated traditional Chinese and Western medicine in the treatment of grade I and grade II post-acute ankle sprains, and serve as the basis for further research.

The authors appreciate their colleagues in Shuguang Hospital Affiliated to Shanghai University of Traditional Chinese Medicine for their full support in recruiting and treating patients. The authors appreciate the efforts and help of investigators participating in this trial. The authors appreciate [name] for his guidance.

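### Two primary pain outcomes share a flat P<0.05 criterion with no success rule, while the sample size covers only VAS at two weeks

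*Protocol article*

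**What the plan says.** The Methods paragraph of the Abstract states: "The main outcome measures are Visual Analog Scale and Short Form McGill Pain Questionnaire". The Primary outcomes section lists the same two. It describes SF-MPQ as having a sensory part and an affective part, and adds that "both pain status and visual analogue scores are now included in the evaluation of overall pain status". No single SF-MPQ score is singled out as the primary one.

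Table 1 schedules both outcomes at baseline, week 2 and 3 months. No section formally declares a primary time point.

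The Statistical analysis section sets the scope and the criterion:

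- "For all outcomes, we will perform intent to treat analysis for our primary assessment of efficacy and a supplementary per protocol analysis"
- "Set α = 0.05 as the significance test level, and when P<0.05, it indicates that the difference is statistically significant"

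It gives no ranking of the two primaries, no split of alpha and no requirement that both succeed.

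The Sample size section uses one quantity, mean VAS after two weeks of treatment (0.04 against 0.25, SD 0.45), with α = 0.05 and β = 0.2. It gives no effect size, SD or power for SF-MPQ.

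**The concern.** Two primary outcomes can be combined in two basic ways. Either one of them is enough to claim effectiveness, or both are needed. The first calls for control of the familywise error. The second calls for a sample size that gives adequate power for both tests together. The article provides neither, so its three statements (two primaries, 0.05 for each test, sizing on one) do not fit together under either reading.

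At stake is what the main result will mean. If VAS and SF-MPQ disagree at week 2, nothing in the text says whether the trial has succeeded, and the choice could be made after the data are seen. This matters more here because, according to the Blinding section, both scales are self-assessed by patients who know their treatment.

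**Working it through.** **Inputs**

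- From Sample size: means 0.25 and 0.04 (difference 0.21), SD 0.45, α = 0.05, β = 0.2, two-sided (the formula uses Z at α/2), n = 72 per group, 20% dropout, 87 per group.
- From the Abstract and Primary outcomes: two primary outcomes.
- From Statistical analysis: each test at 0.05.
- Assumed, because the document gives none: the correlation between the VAS and SF-MPQ test statistics (range 0 to 0.9) and, for the second reading, 80% power for SF-MPQ.

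**Step 1. Reproduce the stated sample size.**

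n = 2 × (1.960 + 0.842)² × 0.45² / 0.21² = 72.08 per group.

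The stated figure is 72. Power at n = 72 is 80.0%. For dropout, 72 × 1.2 = 86.4, rounded up to 87, which is the stated final size. The full two-sided 0.05 is therefore spent on VAS at two weeks, with nothing reserved for a second primary test.

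**Step 2. Reading A: either outcome at week 2 is enough.**

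If the tests are independent, the chance of at least one false-positive primary result is 1 − 0.95² = 0.0975. With correlation r it is 1 − P(|Z1| ≤ 1.96 and |Z2| ≤ 1.96) from the bivariate normal distribution.

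**Step 3. Reading B: both outcomes at week 2 are required.**

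The error for the joint claim cannot exceed that of either single test, so it is at most 5%. Power for the joint claim, with 80% for each test, is 0.80 × 0.80 = 0.64 if independent. With correlation r it is P(Z1 ≤ 0.842 and Z2 ≤ 0.842).

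| Assumed correlation | Reading A: familywise error | Reading B: joint power |
|---|---|---|
| 0 | 9.75% | 64% |
| 0.5 | 9.1% | 69% |
| 0.8 | 7.8% | 73% |
| 0.9 | 7.0% | 75% |

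Across this range, Reading A stays above 5% and Reading B stays below 80%.

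**Step 4. Compare an alpha split.**

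Splitting alpha equally (0.025 for each outcome) would control the error under Reading A. At n = 72, power for VAS would fall from 80.0% to 71.2%. Keeping 80% would need 88 per group before dropout. A fixed order that starts with VAS avoids this loss.

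**The case against.** **The inflation is not established outright.** A reader might infer that the plan's type I error exceeds 5% as it stands. The text does not support that. The Statistical analysis section sets a general significance level and never says that one primary alone establishes effectiveness. If both were required, the error would be controlled. This objection stands, so the excess error is stated here only for Reading A. It does not remove the problem, because Reading B breaks the power statement instead.

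**The 3-month visit.** A reader might also count four primary tests (two outcomes at two times), which would give 18.5% if independent. The document does not support that count either. No section calls 3 months a primary time, the sample size refers to two weeks, and the Follow up section presents the visit as long-term evaluation. Nor is there a flat contradiction about whether the visit takes place. The Design section says "The whole study period will be 2-week including baseline and 2-week treatment" and the Limitation section says "this is an exploratory study that does not involve long-term follow-up to observe long-term treatment outcomes and adverse reactions", but the latter goes on at once to announce a follow-up plan after the protocol ends, in line with the Follow up section ("the research will follow up the patients after 3 months of the treatment"). The wording is clumsy and should be reconciled, but that is a side point.

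**The scales overlap.** Both measure self-reported pain, and the SF-MPQ evaluation takes in a visual analogue score. The independence figure is therefore an upper bound, and about 7% to 8% (correlations 0.8 to 0.9) may be nearer. This stands, but it still leaves the error above 5%.

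**The study is called exploratory and preliminary.** This lowers the severity. It does not supply a decision rule, and the article still sets primary outcomes, a power target and a significance threshold.

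**An analysis plan that is not shown may order the tests.** It may. The point here is not a missing detail: the article itself fixes two primaries, a flat criterion and a sample size for one of them, and these do not agree.

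**Conclusion.** The concern holds in conditional form. The article has two primary outcomes, no success rule, and a sample size built on one of them at the full alpha. If either outcome at week 2 is enough, the familywise error is about 7% to 10% rather than 5%. If both are needed, the error is at most 5% but joint power is about 64% to 75% rather than 80%. The correlations are assumptions, and so is the 80% power for SF-MPQ. If SF-MPQ's own power were lower, joint power would be lower too. None of this depends on the 3-month visit. Given the preliminary aim of the trial, this is a point that should be fixed, not one that invalidates the design.

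**What to change.** Amend the Primary outcomes and Statistical analysis sections as follows:

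- Name VAS at week 2, the outcome and time already used for the sample size, as the single primary test at two-sided 0.05.
- Name one SF-MPQ score in advance and test it at week 2 at two-sided 0.05 only if VAS is significant. Without a named score this second step cannot be run, because the article lists several.
- State that all 3-month results and all other outcomes are secondary and are reported with 95% confidence intervals.

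The sequence holds the error across the two tests at 5%. VAS keeps its full alpha and power, and no extra patients are needed. The cost is that SF-MPQ alone can no longer carry the claim, and that the protocol and the registration need an amendment. Requiring both outcomes, or splitting alpha, would also settle the ambiguity, but each loses power at the current size.

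In the same amendment, align the Design, Follow up and Limitation sections on the status of the 3-month visit.

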### Inclusion criteria

① Those who meet the diagnostic criteria for ankle sprains, in the post-acute period, and have an injury grade of I or II [33];

② Age range from 18 to 35 years old, regardless of gender [34–37];

③ Cumberland Ankle Instability Scale score ≤ 24 points;

④ Those who have not received any other treatment before treatment and are willing to receive conservative treatment shall sign an informed consent form.

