### Sample size

Using data from a previous study [45]. Comparison of sample size estimation formula for two sample means based on bibliometric data, with reference to relevant literature [a] for experimental group VAS (Visual Analog Scale) means μ_2_ = 0.04 after two weeks interventions, while control group VAS (Visual Analog Scale) means μ_1_ = 0.25, the standard deviation σ = 0.45. According to the formula, α = 0.05, β = 0.2, the sample size of each group is calculated to be n = 72, consider a 20% dropout rate, and the final sample size is 87 cases per group.

n1=n2=2×(Zα2+Zβ)2×σ2(μ2−μ1)2

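### Splitting age at 30 within an 18–35 range weakens the age-interaction test if the effect changes gradually with age; testing age in years is a cheap improvement to an exploratory analysis

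*Protocol article*

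**What the plan says.** The Statistical analysis section of the protocol article names four subgroup factors: sex, age, type of injury and sprain grade. For age it specifies "comparing outcomes for participants aged ≤30 versus >30". For effect modification it states: "we use a Wald test of the treatment by subgroup interaction term from a logistic regression model". The significance level is given as "Set α = 0.05 as the significance test level".

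The Inclusion criteria set the "Age range from 18 to 35 years old, regardless of gender". In whole years, the cut therefore compares a band of 13 years (18–30) with a band of 5 years (31–35).

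The Sample size section sizes the trial for the main VAS comparison only. The article gives no power for any interaction test and no expected age distribution. The Limitation section describes the trial as preliminary and exploratory.

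**The concern.** Age is recorded for every participant, because eligibility depends on it. Reducing it to two bands treats an 18-year-old and a 29-year-old as alike, and a 30-year-old and a 31-year-old as different. If the benefit rises or falls gradually with age, the variation within each band is thrown away, and the unequal widths make the loss larger than a central cut would.

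What is at stake is the chance of detecting a gradual age effect in one pre-specified subgroup analysis. An interaction test in a trial sized for its main effect has little power to begin with, so a further loss matters to that question, though to nothing else in the plan.

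**Working it through.** **1. The plan's own figure.** Inputs from the Sample size section: experimental "means μ_2_ = 0.04 after two weeks interventions", control "means μ_1_ = 0.25", SD 0.45, and "α = 0.05, β = 0.2, the sample size of each group is calculated to be n = 72". The printed formula takes the normal quantile at α/2, so the test is two-sided.

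n = 2 × (1.96 + 0.84)² × 0.45² / 0.21² = 2 × 7.84 × 0.2025 / 0.0441 = 72.0 per arm. The stated 72 reproduces, giving 2 × 72 = 144 evaluable.

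**2. Information kept by the split.** For a modifier that acts linearly, the share kept is the squared correlation between age and the indicator of age above 30. Assume whole-year ages 18 to 35, equally likely:

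- variance of age = (18² − 1)/12 = 26.92
- share above 30 = 5/18 = 27.8%
- band means 24 and 33; between-band variance = (5/18)(13/18)(33 − 24)² = 16.25
- share kept = 16.25/26.92 = 0.604, so the loss is 39.6%

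**3. Range over other age distributions (all assumptions).**

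| Ages over 18–35 | Loss |
|---|---|
| Linear rise towards 35 (1:2) | 37% |
| Uniform, whole years | 39.6% |
| Linear decline towards 35 (2:1 to 4:1) | 44–50% |
| Exponential decline (rates 0.1 to 0.2 per year) | 50–63% |
| Bell-shaped, SD 4, mean 28 down to 23 | 47–81% |

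Even the best single cut for uniform ages (after 26) loses 25%.

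**4. Power on the trial's inputs.** Take a linear model on VAS with SD 0.45, N = 144, uniform ages (SD √26.92 = 5.19) and a two-sided 5% test. The standard error of the change in effect from age 18 to 35 is 17 × 2 × 0.45 / (5.19 × √144) = 0.246. With age in years, the expected z is the change divided by 0.246; with the split it is that value times √0.604 = 0.777.

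| Change in effect, 18 to 35 | z, years | z, split | Power, years | Power, split |
|---|---|---|---|---|
| 0.21 | 0.85 | 0.66 | 14% | 10% |
| 0.42 | 1.71 | 1.33 | 40% | 26% |

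Simulation of both tests (8,000 runs, N = 144) gave 13% and 10% for a change of 0.21, and 38% and 25% for 0.42, with error rates near 5% under no interaction. With all 174 analysed, the approximation gives 16% and 11%, then 47% and 31%. With 139 (174 less 20%), it gives 13% and 10%, then 39% and 26%.

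**5. If the effect steps at 30.** Simulated power is 25% with the split and 17% with age in years for a step of 0.21, and 69% and 47% for a step of 0.42. The ordering reverses.

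The power figures use a linear model because a logistic version cannot be computed from the article: the VAS and SF-MPQ are scores, and no binary outcome is defined for them.

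**The case against.** The strongest defence is that the cut is pre-specified and so not driven by the data, that it concerns one of four subgroup factors in a self-described exploratory trial, and that nothing in it is contradictory or miscalculated. This stands, and it is why the point is minor. The lack of a stated reason for choosing 30 also carries no weight, since a condensed article commonly leaves such reasons to the full protocol.

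Second, the direction of the loss depends on the shape of the age effect. If the effect changes abruptly at 30, the planned split is the more powerful test (step 5). This stands as a condition. The article does not say that a step at 30 is expected.

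Third, the improvement is modest in absolute terms, because neither version is likely to detect an age effect of the size considered. This also stands. A reader might infer from the 60% retained that a trend found with 80% power by the split would be found with about 95% power using age in years (2.80/0.777 = 3.60; 3.60 − 1.96 = 1.64). The arithmetic is right, but it does not describe this trial. Reaching 80% power with the split needs a change of 2.80 × 0.246 / 0.777 = 0.89 VAS points across the age range, more than four times the design effect of 0.21.

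**Conclusion.** The point holds conditionally, as a minor one. If effect modification is roughly linear in age, the split at 30 loses about 40% of the information for uniform ages and about 37% to 81% over the other distributions tried. On the planning inputs this lowers power from about 40% to 26% for a change of 0.42 across 18–35, and from about 14% to 10% for a change of 0.21.

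A reader might take the 40% as a fixed property of the plan. The article supports neither condition behind it, since it states no age distribution and no shape for the age effect. Nor does the point cast doubt on the main result: the comparison of the randomised groups does not use the age split. The power figures further assume the planning SD of 0.45 and a linear model on VAS.

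**What to change.** Test the treatment-by-age interaction with age in years, in a model suited to the outcome: a linear model for the VAS and SF-MPQ scores. Keep ≤30 and >30 only to display the treatment estimates by band. Changing the age term but leaving it in the logistic model would not be enough for these scores, as the article gives no binary outcome for that model to use.

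The cost is a sentence or two of analysis wording, with no new data and no extra participants. The downside is that the test assumes a roughly linear change over 18–35 and loses power relative to the split if the effect truly steps at 30. If the investigators have grounds to expect a step there, they should say so and keep the split as the test.

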#### Secondary indicators

① Foot and Ankle Ability Assessment Scale (FAAM) [39,40]. FAAM is a method for assessing the degree of daily living ability limitation and ankle mobility disorders, consisting of 21 scores from daily living activities and 8 scores from the Independent Movement Disorder Scale.

② AOFAS Ankle Posterior Foot Scale [41]. Using the American Orthopedic Foot and Ankle Association (AOFAS) Ankle Posterior Foot Scale as a reliable and effective tool for detecting ankle ligament injuries. This standard consists of two main parts, mainly including pain, function and autonomous activity, support, flexion/extension, inward/outward rotation, ankle and foot stability, etc., with a maximum score of 100 points. The two major scores are each 50 points, with a maximum score of 100 points, excellent (90–100 points), good (75–89 points), average (50–74 points), and poor (<50 points). The larger the score, the better the ankle joint function and symptoms.

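### Subgroup effects are to be tested with logistic regression, but neither primary outcome is binary and no cut-off is defined for either

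*Protocol article*

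**What the plan says.** The Statistical analysis section introduces the subgroup work with "We will perform the following subgroup analyses: sex, men versus women; age, comparing outcomes for participants aged" 30 or under and over 30, and adds sports against non-sports injury and grade 1 against grade 2 sprain. One test serves all four factors: "we use a Wald test of the treatment by subgroup interaction term from a logistic regression model". No outcome is named for that model.

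The abstract states: "The main outcome measures are Visual Analog Scale and Short Form McGill Pain Questionnaire". Under Primary outcomes, the VAS is a 10 cm line and the instruction is "Ask the subjects to mark any position on the horizontal line based on their pain perception"; SF-MPQ items are graded from 0 to 3. Under Secondary indicators, FAAM is described as "consisting of 21 scores from daily living activities and 8 scores from the Independent Movement Disorder Scale", AOFAS is a score with a maximum of 100 that is also banded into four grades, and torque and gait are sets of instrument readings.

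For the main analysis the same section says: "Quantitative data are analyzed using methods such as analysis of variance". The Sample size section compares two mean VAS values.

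**The concern.** The subgroup model and the outcomes do not fit each other. An unqualified logistic model takes a binary dependent variable, and the protocol defines no responder, cure or recovery endpoint. This is not a detail left to a later analysis plan: the article names a specific model, and that model conflicts with the outcome definitions and with the main analysis in the same section.

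Three things are at stake.

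- Someone would have to supply a cut-off for each primary outcome before the test could be run, and nothing in the protocol constrains that choice.
- The interaction would be measured as a ratio of odds ratios for a new endpoint, whereas the trial estimates a difference in means. Interaction depends on scale, so the two need not agree.
- Splitting a score in two generally discards information, and interaction tests have little power to spare.

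**Working it through.** **1. Outcome type against model**

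| Outcome | Scale in the protocol | Binary? | Cut-off defined? |
|---|---|---|---|
| VAS (primary) | position on a 0–10 line | no | no |
| SF-MPQ (primary) | items scored 0–3 | no | no |
| FAAM | 21 + 8 item scores | no | no |
| AOFAS | score up to 100 | no | four ordered bands, limits at 90, 75 and 50 |
| Torque | instrument readings | no | no |
| Gait | instrument readings | no | no |

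Adverse events can be coded yes/no, but they are a safety outcome.

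**2. The plan's own figure is a comparison of means**

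Inputs from Sample size: means 0.25 and 0.04 (difference 0.21), SD 0.45, α = 0.05 two-sided, power 80%.

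n per group = 2 × (1.960 + 0.842)² × 0.45² / 0.21² = 72.08, which the plan states as 72.

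So the planned effect is a mean difference in VAS, and the logistic subgroup test is on a different scale from it.

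**3. Illustration of the power cost**

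Assumptions that are not in the protocol: VAS normal with SD 0.45; 72 analysed per arm; two equal subgroups, so four cells of 36; the full 0.21 effect in one subgroup and none in the other.

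*Linear model.* SE of the interaction = √(4 × 0.45² / 36) = 0.15. Power = Φ(0.21/0.15 − 1.96) = Φ(−0.56) = 0.288, about 29%.

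*Logistic model after a cut at c.* The proportion at or below c is Φ((c − mean)/0.45). The interaction is the log odds ratio in the subgroup with the effect, and its variance is the sum over the four cells of 1/(36 p(1 − p)).

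For c = 0.25: p = 0.500 in three cells and 0.680 in the fourth. Log odds ratio = ln(0.680/0.320) ≈ 0.75. Variance = 3/(36 × 0.25) + 1/(36 × 0.680 × 0.320) ≈ 0.46, so SE ≈ 0.68. Power = Φ(0.75/0.68 − 1.96) ≈ 0.197.

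| Cut on VAS | p at control mean | p at experimental mean | Logistic interaction power |
|---|---|---|---|
| 0 | 0.289 | 0.465 | 18.2% |
| 0.145 | 0.408 | 0.592 | 19.5% |
| 0.25 | 0.500 | 0.680 | 19.7% |
| 0.5 | 0.711 | 0.847 | 17.6% |

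The range is about 18–20%, against 29% for the linear model.

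**4. How far the illustration can be trusted**

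The row for a cut at 0 shows the limit of the normal assumption: it would place 46.5% of the experimental arm below zero, which a 0–10 line does not allow. The figures show the direction and rough size of the loss; they are not a forecast for this trial.

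**The case against.** The best case for the plan has four parts.

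- **Some outcomes could take a logistic model.** The AOFAS bands have fixed limits, so an ordinal logistic model would need no invented cut-off, and adverse events are binary. This stands for those outcomes. A reader might infer that the subgroup analysis cannot be run on anything without an improvised split, and that goes too far. But the text does not say ordinal and does not tie the model to AOFAS, and neither route helps VAS or SF-MPQ.
- **A cut-off need not be chosen to suit the result.** The Blinding section keeps statisticians blinded until the statistics are done, and an analysis plan that is not shown might define responders. So a reader should not infer that a cut-off will be picked with group results in view. Pooled data could still inform it, and the article as it stands gives none.
- **The loss is easily overstated.** A median split of a normal variable keeps 2/π = 64% of the information, and a reader might quote the 36% loss as this trial's. The planning means sit so close to zero that normality is doubtful. Nor would every cut-off leave one category nearly empty. Scores cannot be negative, so a mean of 0.04 allows at most 4% of the experimental arm to reach 1 or more (about 3 of 72), and sparse cells are a real risk for cuts that high. At a cut of 0.25, the normal illustration leaves 50% of controls and 32% of the experimental arm above it.
- **Subgroup tests are supportive.** The trial calls itself exploratory, and even the linear test has only about 29% power in the illustration. This stands, and it limits how serious the point is.

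**Conclusion.** The mismatch is real and lies in the stated text. For both primary outcomes, and for FAAM, torque and gait, the logistic interaction test has no defined dependent variable, and it departs from the comparison of means used elsewhere in the plan. That conclusion rests on the outcome definitions alone and needs no distributional assumption. Only the size of the power loss depends on the assumptions set out in the check.

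It should be fixed, but it is not a threat to the trial's main result: the intention-to-treat comparison, the per-protocol analysis and the sample size do not depend on this sentence.

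**What to change.** Replace the logistic sentence. For continuous outcomes, fit a linear model with treatment, subgroup and their interaction, consistent with the analysis of variance already named. Preferably add the baseline value of the outcome. The protocol does not state that covariate for its main analysis, so this would be an addition, but Table 1 already schedules all six measures at week 0. Report the difference in treatment effect between subgroups with its 95% confidence interval and the interaction P value. If scores pile up at zero, use a robust or bootstrap standard error. Keep logistic regression for outcomes that are truly binary.

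If the investigators do want a responder analysis, the alternative is to fix its outcome, cut-off and time point in advance.

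The cost is one sentence in the analysis section, with no new data and no change to the sample size. It should be settled before anyone sees outcome data.
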